### Blinding

The research team members, with the exception of the clinical research methodology personnel and eligible participants, will be blinded to the treatment allocation. The study code will not be revealed until the end of the study, unless there is a serious adverse event (AE).

This study is a double-blind, double-dummy RCT, and the medicine used for treatment and the placebo will be identical in appearance. In addition, the research team will be instructed not to communicate with the participants regarding their possible treatment group allocation.

### Interventions

The participants in the CHM group will be orally given BMF compound granules (30 mg twice daily) and a placebo for levocetirizine (10 ml/5 mg every night) for 4 weeks. The participants in the control group will be orally given levocetirizine (10 ml/5 mg every night) and a placebo for BMF compound granules (30 mg twice daily) for 4 weeks.

The ingredients, dosage, and pharmacological action of BMF are presented in Table 3 [39]. The placebo for BMF compound granules will be composed of starch and an edible pigment and will be matched as closely as possible to the appearance and taste of BMF. The placebo for the levocetirizine oral solution has the same appearance and dosage as the levocetirizine oral solution but lacks the active ingredient. All interventions will be produced by the manufacturers following good manufacturing practices. The CHM compound granules and CHM placebo will be produced by Jiangyin Tianjiang Pharmaceutical Co., Ltd. (Jiangyin City, Jiangsu Province, China, Good Manufacturing Practice certificate number: JS20140328, batch number: 1608359). Levocetirizine oral solution and its placebo will be produced by Chongqing Huapont Pharmaceutical Co., Ltd. (Chongqing City, China, production license: CQ20130006, batch number: 20160801). All interventions meet the requirements of the regulatory guidelines issued by the China Food and Drug Administration.

**Table 3 Tab3:** Composition and action of *bi min fang*

Ingredients	Percentage (%)	g/sachet	g/day	Action
Radix astragali (*huang qi*)	17.6	7.5	15	TCM: 1 Tonifying the spleen and lung *qi* and increasing *yang*. 2. Strengthening the defense *qi* and securing the exterior. 3. Inducing diuresis and removing edema Pharmaceutical study: 1. Enhancing the immune effect. 2. Inducing diuresis
Rhizoma atractylodis macrocephalae (*bai zhu*)	17.6	7.5	15	TCM: 1 Tonifying the spleen and replenishing *qi*. 2. Eliminating dampness and inducing diuresis. 3. Hidroschesis Pharmaceutical study: 1. Maintaining a strong constitution. 2. Enhancing immunologic function. 3. Inducing diuresis
Radix saposhnikoviae (*fang feng*)	11.8	5	10	TCM: 1. Dispelling wind and releasing the exterior. 2. Dispelling dampness and relieving pain. 3. Stopping convulsions Pharmaceutical study: 1. Antimicrobial and anti-inflammatory effects. 2. Analgesic and anticonvulsive effects
Radix paeoniae alba (*bai shao*)	11.8	5	10	TCM: 1. Nourishing blood and constraining *yin*. 2. Emolliating the liver and relieving pain Pharmaceutical study: 1. Analgesic effect. 2. Antimicrobial and anti-inflammatory effect. 3. Immunologic effect
Herba ecliptae (*mo han lian*)	11.8	5	10	TCM: 1. Enriching the *yin* of the kidney and the liver. 2. Cooling the blood and stopping bleeding Pharmaceutical study: 1. Enhancing immunity. 2. Protecting the liver. 3. Antimutagenic activity
Radix bupleuri (*chai hu*)	11.8	5	10	TCM: 1. Releasing the exterior and abating fever. 2. Soothing liver-*qi* stagnation. 3. Increasing *yang qi* Pharmaceutical study: 1. Inhibiting the central nervous system. 2. Anti-inflammatory and antimicrobial effects. 3. Enhancing immunologic function. 4. Protecting the liver
Xanthii fructus (*cang er zi)*	11.8	5	10	TCM: 1. Dispersing wind and cold. 2. Dispelling dampness. 3. Relieving nasal congestion. 4. Relieving pain Pharmaceutical study: 1. Relieving nasal symptoms. 2. Antimicrobial activity. 3. Preventing coughing
Radix et rhizoma glycyrrhizea (*gan cao*)	5.9	2.5	5	TCM: 1. Tonifying the spleen and replenishing *qi*. 2. Dispelling phlegm and suppressing coughing. 3. Relaxing tension and relieving pain. 4. Clearing heat and detoxifying. 5. Harmonizing medications Pharmaceutical study: 1. Protecting the digestive system. 2. Antiallergic and anti-inflammatory effects

If a participant cannot take the medication for any particular reason, a record will be made, and the medicine will be conserved and returned to the researchers at the end of the study. Two follow-up telephone visits will be performed during the treatment period. Participants who complete treatment will be followed up three times over the course of 3 months (Fig. 2). No other treatment for AR will be allowed for any participant in either group during the study period. The rescue medication, desloratadine tablets (5 mg orally every night, Hainan Poly Pharmaceutical Co., Ltd., Chinese State Food and Drug Administration approval number: H20040972), will be provided for participants who may experience AR episodes. Administration of the rescue medication will be recorded and statistically analyzed as an indicator of a curative effect.

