### Criteria for stopping treatment

A participant may stop treatment and withdraw from the research project for any reason at any time, and the reason for the withdrawal will be recorded in their CRF. The participants will be told that they have the right to withdraw from the trial and that they will be provided with standardized treatment if they withdraw.

The criteria for stopping treatment and withdrawing from the research project are:The participant has suffered an AE related to taking the drug, and the investigator believes it is not appropriate for them to continue taking the drug.The participant is diagnosed with asthma or other complications of AR during the study.The participant develops another severe disease that needs to be treated during the study.Poor compliance, such that the actual drug usage is less than 80% or more than 120% of the prescribed dose.Use of drugs proscribed for AR during the study.

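### The BMF dose in the Interventions text (30 mg twice daily) contradicts Table 3, whose rows sum to 42.5 g per sachet and 85 g per day

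*Protocol article*

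**What the plan says.** In the protocol article, under Interventions, the herbal arm is assigned "BMF compound granules (30 mg twice daily" over 4 weeks. The control arm is assigned "a placebo for BMF compound granules (30 mg twice daily) for 4 weeks", so the 30 mg figure is printed twice. The following paragraph states: "The ingredients, dosage, and pharmacological action of BMF are presented in Table 3".

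Table 3 then lists eight ingredients, each with a percentage, a weight in grams per sachet and a weight in grams per day. It prints no total row. It carries no note on whether the weights refer to raw herb or to finished granule.

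Under Criteria for stopping treatment, one ground for withdrawal is that "the actual drug usage is less than 80% or more than 120% of the prescribed dose".

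**The concern.** The article gives the dose of the investigational product in two places and names the second as the source for dosage. The first is in milligrams, the second in grams, and no statement connects them. The trial's main objective is to assess the efficacy of BMF, and the dose is part of what defines the product under test. A reader who wants to interpret the efficacy or safety result, or repeat the regimen, cannot tell what amount was taken. The placebo is affected in the same way, since its amount is given only by the 30 mg figure.

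**Working it through.** **Inputs.** From the Interventions text: 30 mg per intake, two intakes a day, 4 weeks (28 days). From Table 3, in row order:

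- grams per sachet: 7.5, 7.5, 5, 5, 5, 5, 5, 2.5
- grams per day: 15, 15, 10, 10, 10, 10, 10, 5
- percentages: 17.6, 17.6, 11.8, 11.8, 11.8, 11.8, 11.8, 5.9

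**Step 1: dose by the text.** 30 mg × 2 = 60 mg per day. Over 28 days, 60 mg × 28 = 1,680 mg = 1.68 g.

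**Step 2: dose by Table 3.** Per sachet: 7.5 + 7.5 + (5 × 5) + 2.5 = 42.5 g. Per day: 15 + 15 + (5 × 10) + 5 = 85 g. Over 28 days, 85 g × 28 = 2,380 g.

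**Step 3: is Table 3 consistent with itself?** Dividing each row by 42.5 g gives 7.5/42.5 = 17.65%, 5/42.5 = 11.76% and 2.5/42.5 = 5.88%. These agree with the printed 17.6, 11.8 and 5.9. The printed percentages sum to 100.1, which is rounding. In every row the daily weight is exactly twice the sachet weight, which implies two sachets a day and agrees with the twice-daily schedule in the text. A table that fits together this closely is unlikely to have been damaged when it was read from the PDF.

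**Step 4: text against table, at face value.** Per intake: 42,500 mg / 30 mg = 1,417. Per day: 85,000 mg / 60 mg = 1,417. The smallest ingredient alone: 2,500 mg / 30 mg = 83.

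**Step 5: could Table 3 be raw-herb weight?** The article does not say so. Take it as an assumption, with r grams of raw herb per gram of granule; the range of r from 1 to 10 is also assumed. A sachet then weighs 42.5/r grams.

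| Assumed r | Granule weight per sachet | Multiple of 30 mg |
|---|---|---|
| 1 | 42.5 g | 1,417 |
| 3 | 14.17 g | 472 |
| 5 | 8.5 g | 283 |
| 10 | 4.25 g | 142 |

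For the two figures to agree, r would have to be about 1,417. Even at r = 10 the smallest ingredient alone is 250 mg, about 8 times the stated intake.

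**Step 6: does the compliance rule survive?** Two sachets a day for 28 days is 56 sachets. The limits are 0.8 × 56 = 44.8 and 1.2 × 56 = 67.2 sachets, whatever a sachet weighs. Expressed as an amount of product, the same limits would be 48 and 72 mg per day by the text, or 68 and 102 g per day by Table 3.

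**The case against.** The strongest reply is that the two places may measure different things: the text speaks of compound granules, while Table 3 lists herbs by plant part. If so, 1,417 compares unlike quantities and cannot stand as the size of the error. That is right as far as it goes, and the factor should be quoted only as a face-value ratio. It does not remove the contradiction, because the assumed range up to 10:1 still leaves a gap of about 142-fold.

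A second reply is that a condensed article may leave the yield from herb to granule to the full protocol or product file. This also stands: the absence of a conversion is not the finding. The finding is that two printed figures conflict.

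Three stronger readings are tempting, and the documents do not support them.

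- A reader might infer that the compliance thresholds are undefined. They are relative, and both text and table imply two intakes a day. Untaken medicine is to be recorded and returned, and participants keep a medicine diary. The article does not say that compliance will be judged by sachet count, but it can be.
- A reader might infer that participants were misdosed or put at risk. BMF is packed in sachets and made by a named manufacturer under good manufacturing practice, with a batch number given. Nothing suggests that anyone weighed out doses from the printed text.
- A reader might infer a simple slip of unit. The documents do not establish the cause. Reading the text in grams would give 30 g per intake, which still differs from 42.5 g at face value.

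Nor is any imbalance between arms shown, since the text prints the same figure for BMF and placebo.

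**Conclusion.** The point holds as a contradiction between text and table on the amount of BMF per intake, and the article's own figures suffice to show it. Its size is about 1,417-fold if the Table 3 weights are finished granule, and about 142-fold if they are raw herb at an assumed concentration of 10:1. No value in the assumed range of 1:1 to 10:1 reconciles the two.

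The ingredients, their proportions, the twice-daily schedule and the duration are stated consistently. The sample size, non-inferiority margin, randomization and planned tests do not use the dose and are unaffected. The correction is nevertheless needed, because a result cannot be tied to a dose that is printed with two incompatible values. Which value is right cannot be decided from the article.

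**What to change.** Check the Interventions text and Table 3 against the manufacturer's batch record and correct whichever is wrong. In one place, for BMF and its placebo alike, give the weight per sachet with its unit and say whether it is raw herb or finished granule. If both kinds of weight are reported, give the conversion between them. As a small addition, say that the 80% to 120% rule is applied to sachets taken out of sachets prescribed, if that is the practice. The cost is one check of the batch record and a short text correction; the design and the analysis do not change.

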### Outcome measurement

The primary outcome is a change in the Total Nasal Symptom Score (TNSS) [40]. Secondary outcome measures are as follows: (1) changes in the standard version of the Rhinoconjunctivitis Quality of Life Questionnaire (RQLQ(S)) score; (2) the frequency of AR episodes and their severity (visual analog scale, VAS); (3) changes in the serum levels of cytokines IL-4, interferon-γ (IFN-γ), transforming growth factor β-1 (TGF-β1), and interleukin-17 (IL-17), and changes in the gut microbiota composition in stools before and after treatment. In addition, participants will complete a medicine diary and report any AEs related to the intervention drugs throughout the trial.

The TNSS evaluates the following four nasal symptoms: rhinorrhea, nasal obstruction, nasal itching, and sneezing. The symptoms are self-assessed and recorded by subjects using a four-point scale (0 = no symptoms, 1 = mild symptoms, 2 = moderate symptoms, and 3 = severe symptoms), with low scores indicating less severe nasal symptoms [40]. The RQLQ(S) is a disease-specific questionnaire that can assess quality of life impairment in AR patients. This questionnaire consists of 28 questions covering the following seven domains: activities, sleep, non-nose/eye symptoms, practical problems, nasal symptoms, eye symptoms and emotional problems [41]. The RQLQ(S) with standardized activities is an updated version of the original RQLQ [42]. It has been translated into different languages and has frequently been used in different countries. The VAS, which ranges from 0 (nasal symptoms not at all bothersome) to 10 (nasal symptoms extremely bothersome) was designed to assess the severity of nasal symptom disturbance and has been validated for use in the quantitative evaluation of AR severity [43]. The TNSS, RQLQ(S), and frequency and severity of AR episodes will be evaluated at the beginning of, middle of and after the treatment period and at the end of each month during the 3-month follow-up period (Fig. 2).

Blood and stool samples will be collected before and after the treatment period (Fig. 2). The blood samples will be used to detect the serum levels of the cytokines IFN-γ, IL-4, TGF-β1, and IL-17 using enzyme-linked immunosorbent assays (ELISAs). These cytokines are typical inflammatory cytokines involved in immune disorders and are released by Th1, Th2, T-regulatory, and Th17 cells [44, 45]. To observe the influence of BMF on the composition of the gut microbiota, 16S ribosomal ribonucleic acid (16S rRNA) sequencing will be used to detect bacterial taxa present in stool samples.

A Health and Diet Habits Questionnaire, sampling instructions, a cardboard box, a sampling spoonand a fecal collection tube with cached liquid will be distributed to each participant before the stool samples need to be collected. All participants will be requested to complete the Health and Diet Habits Questionnaire, after which they will be asked to defecate after urinating. The stool will be collected in the cardboard box. The participants will use the sampling spoon to collect two spoonfuls of stool (approximately two grams) without having the sample contact the urine, sewage and fecal pool, and they will deposit the sample in the fecal collection tube. They will then tightly cover the tube and shake it until the sample has uniformly mixed with the cached liquid. The fecal collection tube will keep the stool fresh for 48 h at room temperature. As some participants cannot defecate in a hospital, they will take the above materials home and send their stool samples to the researchers by S.F. Express to arrive within 1 day. All blood samples will be sent to the Biological Resource Center of the GDPHCM within 2 h, and the stool samples will be sent within 24 h. All blood and stool samples will be stored at −80 °C. The 16S rRNA sequencing of the gut microbiota will be performed by BGI Shenzhen Co., Ltd.

Personal information will be collected from potential and enrolled participants by authorized researchers who will be trained at the beginning of the study. Personal information will not be shared without the participants’ agreement.

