### Sample size calculation

This study is mainly focused on determining the efficacy of BMF for AR patients with LSQDS. The primary outcome is the TNSS. With reference to data from a previous study [46] and our clinical observations, the sample size was calculated using the noninferiority test for two means with software PASS 2011. We assumed that the TNSS of the treatment group will be 5.53 ± 2.79 and that of the control group will be 6.64 ± 3.06. To obtain a significance level of 5%, a power of 90%, and a noninferiority margin of 0.92, 74 participants are required. Allowing for an 8% dropout rate, 80 participants are needed, with 40 in each group.

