### Data analysis

All data analyses will be conducted according to the intention-to-treat principle, and the analysis will be performed in a double-blind manner by qualified statisticians. The EpiData 3.1 software will be used to build the database, and missing data will be replaced with the mean or median of the item for the homogeneous participant population according to complete data. Two similar participants with complete data will be subjected to repeated review, and a logic check will be performed to confirm that the data are correct before analysis.

The data will be analyzed using the Statistical Package for the Social Sciences version 17.0 (SPSS 17.0). Measured data will be expressed as the mean, median, minimum, and maximum values. Comparisons between the two groups will be analyzed by analysis of variance and pairwise comparisons (univariate variance will be assessed with the rank-sum test). Count data will be expressed as the composition ratio and the rate. Between-group efficacy will be assessed using the χ^2^ test, and ranked data will be analyzed with the rank-sum test. A baseline comparison test will be performed at a significance level of α = 0.10, and an efficacy analysis will be performed at a significance level of α = 0.05.

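### The primary TNSS change has no named visit among five, is not on the scale of the sample size, and is compared without a baseline covariate

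*Protocol article*

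**What the plan says.** Outcome measurement defines the endpoint as follows: "The primary outcome is a change in the Total Nasal Symptom Score (TNSS". It schedules TNSS "at the beginning of, middle of and after the treatment period and at the end of each month during the 3-month follow-up period". That makes one baseline and five later assessments. The Abstract gives the same definition and schedule. Neither place names a primary visit.

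Sample size calculation drops the word change: "The primary outcome is the TNSS". It assumes that "the TNSS of the treatment group will be 5.53 ± 2.79 and that of the control group will be 6.64 ± 3.06", again with no visit. It uses a noninferiority test of two means with a margin of 0.92, a 5% level and 90% power, and arrives at 74 participants, raised to 80 for dropout.

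Data analysis says: "Comparisons between the two groups will be analyzed by analysis of variance and pairwise comparisons". It also mentions the rank-sum test. It names no visit and no baseline covariate. Baseline appears there only in this sentence: "A baseline comparison test will be performed at a significance level of α = 0.10".

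**The concern.** A primary outcome needs a variable, a time point and an analysis that fit one another. Here the variable is a change in one section and a level in another, and the time point is not given in either.

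The missing visit matters most. The five candidates do not answer one question: two concern the effect during or at the end of the 4 weeks of treatment, and three concern what remains up to 12 weeks after it. A statement that BMF is noninferior could mean either. If the visit is left open until the data are seen, the claim can rest on the most favourable one, and the 5% level no longer holds.

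The second matter is efficiency. Baseline TNSS is collected on everyone. Subtracting it uses it less well than fitting it as a covariate. Testing it for imbalance at 0.10 does not use it at all: under randomization any baseline difference is due to chance, and the test neither corrects it nor adds precision.

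**Working it through.** **Inputs from Sample size calculation.** BMF 5.53 (SD 2.79), control 6.64 (SD 3.06), margin 0.92, level 5%, power 90%, 74 evaluable.

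**Inputs assumed, because the article does not give them.** The baseline-to-visit correlation ρ (0.3 to 0.7), a baseline SD equal to the planning SD, and the correlation between test statistics at different visits (0.3 to 0.7).

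**1. Reproducing the 74.**
- Pooled SD = √[(2.79² + 3.06²)/2] = √8.574 = 2.928.
- Lower TNSS is better, so the assumed benefit is 6.64 − 5.53 = 1.11, and the distance from the margin is 0.92 + 1.11 = 2.03.
- With 37 per arm, SE = 2.928 × √(2/37) = 0.681 and the noncentrality is 2.03/0.681 = 2.98. At one-sided 5% the noncentral t gives power 90.5%, and 37 is the smallest group size that reaches 90%. So 74 is reproduced.
- At one-sided 2.5% the same calculation needs 45 per arm, so the stated 5% is one-sided in effect.

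**2. Which scale the 74 is on.** If 5.53 and 6.64 were reductions from baseline, BMF would be worse by 1.11. That lies beyond the 0.92 margin, and no sample size could show noninferiority. The calculation therefore uses absolute scores.

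**3. What carries over to a change score.** Under randomization the expected difference in change equals the expected difference in final score, so 1.11 and 0.92 stay valid. The SD does not carry over:
- unadjusted change: SD × √[2(1 − ρ)]
- ANCOVA: SD × √(1 − ρ²)

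The ratio of the ANCOVA variance to the change variance is (1 + ρ)/2, which is below 1 for every ρ below 1. The change-score SD equals the planning SD when 2(1 − ρ) = 1, that is, at ρ = 0.5.

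**4. Power at 37 per arm, one-sided 5%, distance 2.03.** An unadjusted final score has 90.5% whatever ρ is.

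| ρ | SD of change | SD, ANCOVA | Power, change | Power, ANCOVA |
|---|---|---|---|---|
| 0.3 | 3.465 | 2.793 | 80.3% | 92.7% |
| 0.4 | 3.208 | 2.684 | 85.3% | 94.3% |
| 0.5 | 2.928 | 2.536 | 90.5% | 96.1% |
| 0.6 | 2.619 | 2.342 | 95.1% | 98.0% |
| 0.7 | 2.268 | 2.091 | 98.5% | 99.4% |

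**5. Error if any of five visits may carry the claim.** Each visit is tested at one-sided 5%, with the true difference exactly at the margin at every visit. The error is the probability that the largest of five equally correlated standard normal statistics exceeds 1.645 (one million simulated draws):
- correlation 0.3: 19.3%
- correlation 0.5: 16.6%
- correlation 0.7: 13.5%
- independent visits, as an upper reference: 1 − 0.95⁵ = 22.6%
- one named visit: 5%

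**The case against.** The strongest reply is that much of this may be settled elsewhere. The article is condensed, the analysis plan is not shown, and the Data analysis section describes measured data in general. Naming analysis of variance does not exclude a covariate or a time factor. That is fair for the model terms, and it is why the ANCOVA part is an improvement rather than an error. It does not cover the visit, which is part of the definition of the primary outcome, nor the two scales, which the article itself states.

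Four stronger readings are tempting, and the article does not support them.

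- A reader might infer that the mismatch leaves the trial underpowered. Against the planned 90%, a change score loses only below a correlation of about 0.5. At 0.6 and 0.7 it exceeds the plan. The article gives no correlation.
- A reader might compute the error over five visits at two-sided 5% and obtain about 15% to 21%. The trial is sized as a one-sided noninferiority test, and a two-sided rate also counts false results in favour of the control. The one-sided range is the relevant one. Even that range assumes a difference at the margin at all five visits, although three fall after treatment ends.
- A reader might say that baseline is ignored. A change from baseline does use it, only less efficiently than a covariate.
- A reader might fear that the 0.10 test steers the primary analysis. Nothing in Data analysis makes the analysis depend on its result.

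**Conclusion.** The point stands in limited form, as something that should be changed. The article names no primary TNSS visit among five that differ in kind, and it defines a change while sizing the trial on levels. Both follow from its text without outside assumptions.

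The sizes are conditional. Free choice of visit would raise a one-sided 5% error to about 14% to 19%, given between-visit correlations of 0.7 to 0.3 and a true difference at the margin throughout. This measures what the wording leaves open; it is not evidence that anyone intends to choose. Relative to ANCOVA, an unadjusted change score gives up about 12 percentage points of power at ρ = 0.3, about 6 at 0.5 and about 1 at 0.7, with equal baseline SD and the planned benefit of 1.11. Whether it misses the planned 90% cannot be decided from the article.

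**What to change.** Before unblinding, state the following:

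- One primary visit, for example the end of the 4-week treatment.
- The primary comparison is TNSS at that visit by ANCOVA with baseline TNSS as covariate. Noninferiority is judged by setting the confidence limit of the adjusted difference against the 0.92 margin, with the one-sided level stated.
- TNSS at all other visits is secondary.
- The means and SDs in Sample size calculation refer to the absolute score at the primary visit, so that outcome, analysis and sample size are on one scale.

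As a minor tidy-up, report baseline data descriptively instead of testing them at 0.10.

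The cost is wording in the protocol and analysis plan. No visit, measurement or participant is added, and the sample size need not change: with ANCOVA, 37 per arm has at least 92.7% power over the correlations shown, under the article's own planning assumptions. Trial status reports 76 participants recruited by 7 November 2017, so the change should be dated and shown to precede unblinding.
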